### Statistical Analysis

Primary analysis will compare scores on the GHQ-12 and 5 key heiQ dimensions (emotional support and well-being; monitoring and insight; constructive attitudes; skill acquisition; health service navigation) at a 6-month follow-up across the 3 groups. Differences between treatment groups on each of GHQ-12 and heiQ scores at the 6-month follow-up will be tested using analysis of covariance. The outcomes in the models will be the GHQ-12 score and heiQ score of interest at 6 months, the main predictor of interest will be treatment group and the baseline value of the GHQ-12 score and heiQ score will be included as covariates. Three post-hoc contrasts will be carried out; the first 2 of these will compare separately each of the intervention groups with the control group and the third will compare the proactive telephone-delivered support with the proactive Web-delivered support. To account for Type I error in the post-hoc analyses, Bonferroni corrections will be applied.

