In the context of the CIS service, the most appropriate first step for testing Web approaches may be via a proactive and personalized, rather than automated, version of the service through email and live chat. Email counseling involves the patient and counselor exchanging questions and responses at the frequency of their choosing over the Internet. Live chat involves typed interactive conversations occurring in real-time over the Internet. Evidence for online peer-support forums and email is promising with a RCT of a multicomponent Web intervention reporting decreased global severity scores in a sample of 325 breast and prostate cancer patients [31]. However, there is no literature regarding Internet-delivered versions of low-intensity community-based support akin to that offered by the CIS service. For example, a Cochrane review examining the effects of email and Web-messaging between patients and health professionals was unable to establish the benefits of such Web-based platforms due to the lack of high-quality studies identified [32]; relevant to this study, none of the 9 reviewed articles included cancer samples.

This multisite, blinded, patient-RCT will be the first to conduct a robust study of the relative merits of telephone- versus Web-based methods for providing low-intensity information and support to people affected by cancer. Newly diagnosed lung cancer patients will be recruited by health professionals and randomly-allocated on a 1:1:1 ratio to 1 of 3 arms: (1) a printed information booklet, (2) proactive telephone-delivered support, or (3) proactive Web-delivered support. The Consolidated Standards of Reporting Trials of Electronic and Mobile HEalth Applications and onLine TeleHealth is used to describe this study [33].

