### Randomization Process and Blinding

Stratified block randomization will be completed by the research team using a Web-based random number generator program immediately upon receiving a completed consent form. All participants will complete the baseline survey prior to randomization. Randomization will be by patient, with analyses accounting for clustering of outcomes by CIS consultant. The randomized list of patients will then be given daily to the CIS service to contact participants using the allocated approach method (mailed booklet, telephone call, or email/live chat). Due to the nature of the interventions, patients and CIS consultants will not be blinded to the allocation arm; health professionals will not be informed of participants’ allocation. Those responsible for data analysis and interpretation will be blind to group allocation. There is no foreseeable circumstance in which revealing a participant's group allocation to data analysts would be required.

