### Sample Size

The sample size calculation is based on the post-hoc contrasts. The comparison of each intervention group with minimal ethical care is a superiority analysis, whereas the comparison of the 2 intervention arms of the study is a noninferiority analysis.

The study aims to recruit 501 subjects, and therefore complete data will be available for approximately 375 patients (125 per arm) at 6 months with an estimated 25% (125/501 participants) lost to follow-up. This sample size will provide the study with more than 80% power to detect a difference between each of the intervention groups and the control group of 0.35 SD at an alpha level of 0.01 assuming the correlation between baseline and follow-up scores is at least 0.7. This sample size will also provide the study with 90% power to claim noninferiority in the comparison between the 2 interventions if the true underlying difference between the groups is 0.29 SDs for either the heiQ or GHQ-12. A meta-analysis of Web-based emotional support reported an average effect size of approximately 0.4 across 15 studies [48]; similarly, previous research found modest effect sizes of 0.3-0.5 on the heiQ in self-management interventions in Australian and hospital-based samples [49,50]. The age group and gender of nonparticipants will be compared with that of participants to assess nonconsent bias.

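### Randomisation is stratified, but the stated ANCOVA terms include no stratification factors; if the strata are prognostic, the reported standard errors will be too large and the tests mildly conservative

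*Protocol article*

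**What the plan says.** Under Randomization Process and Blinding, the article says "Stratified block randomization will be completed by the research team using a Web-based random number generator program". It does not say there or elsewhere which factors define the strata. Allocation is "randomly-allocated on a 1:1:1 ratio to 1 of 3 arms" (Background).

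Under Statistical Analysis, differences in GHQ-12 and heiQ scores at 6 months "will be tested using analysis of covariance". The article then sets out the model: the outcome is the 6-month score, and "the main predictor of interest will be treatment group and the baseline value of the GHQ-12 score and heiQ score will be included as covariates". That section goes on to set three contrasts and a Bonferroni correction.

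One more feature of the analysis stands only in the randomisation section: "Randomization will be by patient, with analyses accounting for clustering of outcomes by CIS consultant".

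Taken together, the stated model has treatment group, baseline score and an allowance for consultant clustering. Stratification factors are not among its terms.

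**The concern.** Stratified allocation forces the arms to be alike on the stratification factors. If those factors predict outcome, differences between strata no longer contribute to the chance variation of the treatment contrast. A model without the strata still counts those differences as residual error. It therefore reports a standard error larger than the true sampling variation of the estimate.

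The consequences are a test whose actual size is below nominal, some power forgone, and a confidence interval for the Web-versus-telephone noninferiority comparison that is wider than it need be. None of these makes a false positive more likely.

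The consultant adjustment does not close the gap. Consultants deliver the support after allocation, and the control arm is mailed a booklet with no planned consultant contact (Arm 1: Minimal Ethical Care). A consultant term therefore does not stand in for the randomisation strata.

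**Working it through.** **Inputs from the article**
- Completers: "complete data will be available for approximately 375 patients (125 per arm) at 6 months", "with an estimated 25% (125/501 participants) lost to follow-up". Check: 501 × 0.75 = 375.75.
- Correlation between baseline and follow-up: at least 0.7 (Sample Size).
- Superiority: 0.35 SD at alpha 0.01, power above 80% (Sample Size). The hypothesised effect is 0.30 SD (Hypotheses).
- Noninferiority: 0.29 SD, 90% power (Sample Size).

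**Assumptions**
- The 0.01 level is two-sided.
- For noninferiority, 0.29 SD is the margin, the true difference is zero, and the test is one-sided at 0.025.
- R² is the share of residual variance (after baseline score) explained by the strata. The article does not give it, and it cannot be derived because the factors are unnamed. Values of 0, 0.02, 0.05 and 0.10 are used.

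**Step 1: reproduce the plan's power without strata**

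Residual variance = 1 − 0.7² = 0.51. SE₀ = √(2 × 0.51/125) = 0.0903 SD.

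- Superiority at 0.35 SD: Φ(0.35/0.0903 − 2.576) = 90.3%, which satisfies the claim of more than 80%.
- Noninferiority at 0.29 SD: Φ(0.29/0.0903 − 1.96) = 89.4%, close to the stated 90%.
- Superiority at 0.30 SD: Φ(0.30/0.0903 − 2.576) = 77.2%.

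The stated powers are therefore met with baseline adjustment alone.

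**Step 2: effect of omitting the strata**

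With balanced strata, the true standard error is SE = SE₀√(1 − R²), while the model without strata still reports about SE₀.

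- Actual size, strata omitted = 2[1 − Φ(2.576/√(1 − R²))]
- Power at 0.30 SD, strata omitted = Φ((0.30 − 2.576 × SE₀)/SE)
- Power at 0.30 SD, strata included = Φ(0.30/SE − 2.576)

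| R² (assumed) | Reported SE / true SE | Actual size at 0.01 | Power at 0.30 SD, omitted | Power at 0.30 SD, included |
|---|---|---|---|---|
| 0 | 1.000 | 0.0100 | 77.2% | 77.2% |
| 0.02 | 1.010 | 0.0093 | 77.4% | 78.2% |
| 0.05 | 1.026 | 0.0082 | 77.8% | 79.7% |
| 0.10 | 1.054 | 0.0066 | 78.4% | 82.2% |

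The power forgone at 0.30 SD is 0, 0.8, 1.9 and 3.8 points. At 0.35 SD, power is 90.9% omitted against 91.9% included at R² = 0.05, and 91.5% against 93.4% at R² = 0.10. For noninferiority the pairs are 90.0% against 90.9%, and 90.6% against 92.3%.

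**Step 3: simulation check**

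The formulas assume exact balance, which incomplete blocks and dropout erode. A simulation with 6,000 runs per setting (assumed: four strata, blocks of six, three arms, 501 patients, 25% random dropout) gave the same picture. At R² = 0.10 the mean reported SE was 0.0905 without strata and 0.0859 with them, and null rejection at the 0.01 level was 0.006 against 0.009. At R² = 0 the two models were practically the same.

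**The case against.** The strongest objection is that the article is a condensed account and does not put every model feature in one place. The consultant adjustment appears only in the randomisation section, so silence about strata under Statistical Analysis does not prove that they will be left out. A full protocol or SAP may name the factors and include them. This part stands: a reader might infer that the model is deliberately confined to treatment and baseline score, and the article does not support that. Even so, it goes beyond naming a method. It lists the outcome, predictor, covariates, contrasts and multiplicity correction, and that list omits the factors by which patients are randomised. The published specification can be judged as written.

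A second objection is that the harm cannot be demonstrated. This also stands. With unnamed factors, R² could be zero, for example if the strata carry nothing beyond the baseline score, and then nothing is lost.

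Third, a reader might infer that the precision gained by stratifying is thrown away, or that this omission leaves the trial underpowered. Neither follows. The arms remain balanced, and power without strata rises slightly with R² (77.2% to 78.4% at 0.30 SD). What is missing is the reflection of the gain in the reported standard error. The sample size takes no credit for stratification, and its stated power at 0.35 SD is met without it. The 77% at 0.30 SD comes from the gap between the hypothesised effect and the one used for sizing, which is a separate matter.

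**Conclusion.** The point holds in a conditional and modest form. Randomisation is stratified and the stated ANCOVA terms do not include the strata. If the strata predict the 6-month score beyond baseline, the reported standard errors are too large, by about 1.0, 2.6 or 5.4% at an assumed R² of 0.02, 0.05 or 0.10, and the tests are mildly conservative. At the top of that range, including the strata would move power at the hypothesised 0.30 SD from just below 80% to just above it. At R² = 0 there is no effect.

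The figures rest on 125 completers per arm, a correlation of 0.7, a two-sided 0.01 level and the assumed R² values. The error is in the safe direction.

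**What to change.** Name the stratification factors and add them as covariates to the primary ANCOVA models and to the secondary-outcome models, alongside baseline score and the consultant adjustment. If health service is one of the factors, enter it as a random effect: with 50 services and about 375 completers there would be on average 7.5 per service, or 2.5 per arm, which is thin for 49 fixed effects.

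The cost is one phrase in the analysis section and, with a small number of strata, a few degrees of freedom out of about 375. No new data are needed beyond the factors already recorded for randomisation. Fixing this before outcomes are analysed also removes a later choice between adjusted and unadjusted results. If the full protocol or SAP already includes the strata, it is enough to bring the published description into line with it.

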**Emotional adjustment**				
	The Mental Adjustment to Cancer Scale [36]	X		

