**Disease/treatment**				
	Date of cancer diagnosis; cancer type; other comorbid conditions; surgery and treatments received; and history of mental health treatment prior to cancer diagnosis	X		
	Current extent of cancer; surgery and treatments received; and instances of missed prescriptions in previous week		X	X

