##### Antecedent and Moderating Factors

Participants will complete additional survey items to account for sociodemographic, disease and treatment, and social support characteristics, which may moderate the intervention effects. Table 1 outlines these survey items, along with all study data items, and the time-point at which this information will be collected.

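### The primary ANCOVA is valid, but its only patient-level covariates are the baseline scores; a short prespecified set of other pre-randomization covariates would add modest precision at little cost

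*Protocol article*

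**What the plan says.** The Statistical Analysis section sets the method: differences between groups on GHQ-12 and "heiQ scores at the 6-month follow-up will be tested using analysis of covariance". On the terms of the model it says that "the main predictor of interest will be treatment group and the baseline value of the GHQ-12 score and heiQ score will be included as covariates". No further patient-level covariate is named. The section on randomization and blinding adds that analyses will account for clustering by CIS consultant. It also says that every participant completes the baseline survey before being randomized.

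Table 1 shows what that survey contains besides the primary outcomes. Its disease and treatment row lists "Date of cancer diagnosis; cancer type; other comorbid conditions; surgery and treatments received; and history of mental health treatment prior to cancer diagnosis". Its emotional adjustment row lists "The Mental Adjustment to Cancer Scale". Social support and illness perception scales are also collected at baseline. The section on antecedent and moderating factors says the additional items are there "to account for sociodemographic, disease and treatment, and social support characteristics, which may moderate the intervention effects".

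The Sample Size section bases power on 125 completers per arm, a baseline to follow-up correlation of at least 0.7 and alpha 0.01, with 25% lost to follow-up.

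**The concern.** Eligibility covers any lung cancer type, including mesothelioma, and anyone less than 4 months from diagnosis. In so mixed a group, distress and self-management scores at 6 months plausibly depend on type of disease, time since diagnosis and psychological history, even at a given baseline score. The documents do not quantify this. If it is so, variance that could be removed with data already in hand stays in the error term and widens the interval for all three contrasts, both superiority and noninferiority.

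The second issue is missing data. A quarter of participants are expected to be lost, in a disease where the Measures section puts life expectancy below 12 months for about 60% of patients. An analysis of completers that conditions only on arm and baseline score must assume that loss is unrelated to the 6-month score given those two things. Conditioning also on disease type and time since diagnosis would relax that assumption somewhat.

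**Working it through.** **Inputs.** From the Sample Size section: n = 125 completers per arm, r = 0.7, alpha 0.01 (taken as two-sided; the article does not say), difference 0.35 SD. From the Hypotheses section: difference 0.30 SD. Noninferiority: 0.29 SD read as the margin, with true difference 0 and one-sided 2.5% (assumptions). The added covariates explain a share p of the residual variance; p is not in the documents, so a range is shown.

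**Formulas.** In SD units, SE = sqrt(2 × (1 − r²) × (1 − p) / n). Superiority power = Φ(d/SE − 2.576). Noninferiority power = Φ(0.29/SE − 1.960).

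**The plan's own figures (p = 0).** SE = sqrt(2 × 0.51/125) = 0.0903. For 0.35 SD: 0.35/0.0903 − 2.576 = 1.299, power 90.3%, consistent with the stated figure of more than 80%. With no baseline adjustment it would be 57.6%, so the plan depends on the baseline-score ANCOVA and that model delivers. Noninferiority power is 89.4%, matching the stated 90%.

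**With added covariates, r = 0.7:**

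| p (assumed) | SE | SE reduction | Power, 0.35 SD | Power, 0.30 SD | Equivalent n per arm, 125/(1 − p) |
|---|---|---|---|---|---|
| 0 | 0.0903 | – | 90.3% | 77.2% | 125 |
| 0.02 | 0.0894 | 1.0% | 91.0% | 78.2% | 127.6 |
| 0.05 | 0.0880 | 2.5% | 91.9% | 79.7% | 131.6 |
| 0.10 | 0.0857 | 5.1% | 93.4% | 82.2% | 138.9 |

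Noninferiority power rises from 89.4% to 90.9% at p = 0.05 and 92.3% at p = 0.10.

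**If the correlation falls short.** With r = 0.5, below the plan's assumption, SE at p = 0 is sqrt(2 × 0.75/125) = 0.1095. Power at 0.30 SD is then 56.5%, rising to 59.3% at p = 0.05 and 62.2% at p = 0.10. The added covariates recover only a small part of that shortfall.

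**The case against.** The strongest reply is that nothing here is wrong. ANCOVA on the baseline score is a standard, unbiased analysis of a patient-randomized trial. It is the model on which the sample size rests, and it meets the stated power at 0.35 SD. All of that stands.

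A reader might infer that the plan contradicts itself, promising in the section on antecedent and moderating factors to account for patient characteristics and then leaving them out of the model. The full sentence does not support this: it presents the items as possible moderators, which concerns effect modification and makes no promise about the primary model. A reader might also infer bias from the omission; randomization rules that out for the comparison as such. Nor is the baseline score the only thing the analysis allows for. Consultant clustering is stated, and the covariate sentence can be read as putting both baseline scores in each model, which would leave less for other psychosocial scales to explain.

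The size of the gain rests on an assumed p. At 2% it is about one point of power. The missing-data benefit is plausible but not demonstrated, and current extent of cancer, a likely driver of death and non-return, is listed in Table 1 only at 3 and 6 months.

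Finally, a condensed article may leave further covariates to an analysis plan that is not shown. That limits the weight of the point. It does not remove it, because the article does state the covariates of the primary model.

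**Conclusion.** The point holds as a low-cost improvement to a sound model. The article names no patient-level covariate beyond the baseline GHQ-12 and heiQ scores, while other plausibly prognostic measures are in hand before randomization. The consequence is a modest loss of precision and a narrower missing-at-random assumption.

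Under an assumed 2 to 10% of residual variance explained, the gain is worth about 3 to 14 completers per arm. It matters little at the 0.35 SD used for sample size, where power is already about 90%. It matters more at the 0.30 SD that the trial hypothesises, where baseline-only power is just under 80%. These figures assume 125 completers per arm and a two-sided 0.01 test, and they ignore consultant clustering.

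**What to change.** Before unblinding, name a short set of additional baseline covariates for the primary model. Reasonable examples are cancer type as recorded, time since diagnosis and prior mental health treatment. State how missing covariate values will be filled by a simple imputation, and keep the stated adjustment for consultant clustering. Report the model with baseline scores only as a sensitivity analysis. If the psychosocial scales are considered as well, choose among them on stated grounds and keep the list short.

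The cost is a few lines in the analysis plan. If cancer type has three categories and the other two covariates take one term each, that is about four degrees of freedom out of some 370. Some covariate values will need imputing; no new data are collected. The change does not deal with patients who die before 6 months, which needs its own handling.

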### Hypotheses

It is hypothesized that at 6 months follow-up: (1) those in the 2 experimental conditions (proactive telephone-delivered or Web-delivered support) will have GHQ-12 scores that are 0.3 of a standard deviation (SD) lower than those for the control condition and heiQ scores that are 0.3 of a SD higher than those for the control condition, and (2) those in the proactive Web-delivered support condition will have heiQ scores within 0.29 of a SD of those in the proactive telephone-delivered support condition.

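### Holm's step-down procedure on the same three contrast p-values would keep the family-wise error of the planned Bonferroni correction and give more power

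*Protocol article*

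**What the plan says.** The Statistical Analysis section compares the three arms at 6 months by analysis of covariance and then sets out the contrasts: "Three post-hoc contrasts will be carried out; the first 2 of these will compare separately each of the intervention groups with the control group". The third contrast sets telephone against Web. On multiplicity it says only: "To account for Type I error in the post-hoc analyses, Bonferroni corrections will be applied". It gives no family-wise alpha and does not say which tests form the family.

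The Sample Size section bases the sample size on these contrasts and gives their type: "The comparison of each intervention group with minimal ethical care is a superiority analysis". Web against telephone is instead to be assessed for noninferiority. The superiority contrasts are sized for "more than 80% power to detect a difference between each of the intervention groups and the control group of 0.35 SD", at alpha 0.01, with a baseline to follow-up correlation of at least 0.7 and 125 analysed per arm. The noninferiority contrast is given 90% power with a figure of 0.29 SD. The Hypotheses section expects a smaller superiority effect than the sizing does: "GHQ-12 scores that are 0.3 of a standard deviation (SD) lower than those for the control condition", and the same 0.3 SD on the heiQ.

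**The concern.** Single-step Bonferroni tests every contrast at one third of the family alpha, whatever the other contrasts show. Holm starts at the same level for the smallest p-value. After each rejection it relaxes the level for the next, to one half of alpha and then to the full alpha. It needs no assumption about how the tests are correlated, so the shared booklet arm and the mix of superiority and noninferiority hypotheses do not affect its validity.

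The first aim rests on the two support-versus-booklet contrasts, and the first hypothesis expects both modes to beat the booklet. The second aim rests on the third contrast. If the hypotheses are roughly true, several of the three nulls are false, and that is when a step-down procedure helps most. A procedure that never rejects more than another, at the same error level, makes it more likely that one of the two booklet contrasts is missed.

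**Working it through.** **Inputs from the protocol article.** 125 per arm, correlation 0.7, sizing effect 0.35 SD and alpha 0.01 (Sample Size); hypothesised effect 0.30 SD (Hypotheses); three contrasts, two of superiority and one of noninferiority (Statistical Analysis and Sample Size).

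**Assumptions.** Family alpha 0.05 over the three contrasts of one score; two-sided superiority tests; 0.29 SD as the noninferiority margin with a true Web-telephone difference of zero; equal true effects in both support arms.

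**1. Standard error of a contrast.** SE = sqrt(2 × (1 − 0.7²) / 125) = sqrt(2 × 0.51 / 125) = 0.0903 SD.

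**2. The plan's own figures.**
- Numbers: 501 / 3 = 167 per arm, and 167 × 0.75 is about 125.
- Superiority at 0.35 SD, two-sided 0.01: Φ(0.35/0.0903 − 2.576) = Φ(1.30) = 90.3%. This agrees with the stated figure of more than 80%.
- Noninferiority, one-sided 0.025 without correction: Φ(0.29/0.0903 − 1.960) = Φ(1.25) = 89.4%. This agrees with the stated 90%.

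**3. Bonferroni over three at family alpha 0.05.** The two-sided critical value at 0.05/3 is 2.394.
- Superiority at 0.30 SD: Φ(3.321 − 2.394) = 82.3%.
- Superiority at 0.35 SD: Φ(3.875 − 2.394) = 93.1%.
- Noninferiority at one-sided 0.025/3: Φ(3.210 − 2.394) = 79%. At one-sided 0.05/3: Φ(3.210 − 2.128) = 86%.

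**4. Holm on the same three p-values.** The three arm means were simulated with the standard error above (at least 200,000 trials per scenario). The third contrast entered with its noninferiority p-value, either doubled (one-sided 0.025 scale) or as it stands (one-sided 0.05 scale).

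| True effect 0.30 SD in both support arms | Bonferroni | Holm |
|---|---|---|
| Each booklet contrast | 82% | 88-90% |
| Both booklet contrasts | 72% | 83-84% |
| Noninferiority, one-sided 0.025 scale | 79% | 88% |
| Noninferiority, one-sided 0.05 scale | 86% | 92% |

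The upper end of 88-90% is the telephone contrast and the lower end the Web contrast. The chance of failing to win both falls from 28% to 16-17%. At 0.35 SD, each booklet contrast goes from 93% to 96-97%.

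**5. Sensitivity.**
- If the third contrast is run as a plain difference test with no true difference, Holm reaches only 85% per booklet contrast and 77% for both at 0.30 SD.
- If the family alpha is 0.03, so that each Bonferroni test sits at the planning level of 0.01, 77% per contrast and 65% for both become about 83-85% and 77% (noninferiority version).

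**6. Bounds and error.** No procedure at a family alpha of 0.05 can exceed an unadjusted test at 0.05. That gives 91.3% at 0.30 SD and 97.2% at 0.35 SD, so the gain for a single booklet contrast is at most 91.3 − 82.3 = 9.0 points and 97.2 − 93.1 = 4.1 points (4.2 before rounding). With all three run as difference tests under the global null, the simulated family-wise error was 4.4% for both Bonferroni and Holm.

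**The case against.** The strongest reply is that Bonferroni is a valid correction and contradicts nothing in the document. The superiority contrasts were sized at alpha 0.01, which is stricter than 0.05/3 = 0.0167, and still reach 90% at 0.35 SD. Even at 0.30 SD, Bonferroni at 0.05/3 gives 82%. This stands: there is no shortfall against the stated superiority power, and a reader who inferred that Bonferroni leaves those comparisons underpowered would be going beyond the document.

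A second reply is that Bonferroni buys something. It yields simple simultaneous confidence intervals, which matter for a contrast judged against a margin of 0.29 SD. This also stands, so the power is not given up for nothing.

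A third reply is that the family and its alpha are not stated, and an article may leave them to the analysis plan. This limits the figures, which are conditional on the alphas shown. It does not affect the ordering, because Holm rejects at least as much as Bonferroni over any family.

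A reader might also infer a loss of up to 13 points. That figure is 85% − 72%: power to win both booklet contrasts when these two are tested as their own family by Holm or step-down Dunnett. It is not a loss for one comparison, and it does not come at the same error level. With telephone 0.29 SD above the booklet and Web equal to it, two nulls are true. Spending the full 0.05 on the booklet contrasts and testing noninferiority separately then gives a family-wise error of 6.4% at one-sided 0.025 and about 8.7% at one-sided 0.05.

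**Conclusion.** The point holds as an efficiency gain. Plain Bonferroni is named for three fixed contrasts, and Holm on the same p-values is uniformly at least as powerful at the same family-wise error. Under the assumptions listed, the gain at the hypothesised 0.30 SD is about 6 to 7 points per booklet contrast, 11 to 12 points for winning both, and 6 to 9 points for noninferiority. At the sizing effect of 0.35 SD it is about 3 to 4 points per booklet contrast. The figures would change with the family alpha, with the correlation, and with whether the third contrast is run as a noninferiority test. The document does not support calling the plan invalid or short of its stated superiority power.

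**What to change.** In the Statistical Analysis section, replace the sentence on Bonferroni corrections with: *Holm's step-down procedure will be applied to the same contrast p-values, with the Web-versus-telephone contrast entering with its noninferiority p-value.* Apply it over whatever family the Bonferroni correction was meant to cover, and keep all three contrasts in that family. State whether the one-sided noninferiority p-value is doubled before it enters, since this sets its level (one-sided 0.025 or 0.05 scale).

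The cost is one sentence, fixed before unblinding, with no extra patients. The one drawback is that Holm gives no simple simultaneous confidence intervals. Bonferroni-wide or unadjusted intervals, labelled as such, should be reported beside the Holm p-values.
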